#### 8.4.2 Causal Relationship

The investigator will evaluate each AE that occurred after administration of the IMP regarding the **relationship** with the IMP:

|             |                                                                                                                                                                                         |
|-------------|-----------------------------------------------------------------------------------------------------------------------------------------------------------------------------------------|
| Related     | There is a reasonable possibility of a causal relationship between the event and the IMP, i.e. the possibility for a causal relationship between the IMP and the AE cannot be excluded. |
| Not related | There is no reasonable possibility of a causal relationship between the AE and the respective IMP, i.e. there is a clear alternative explanation.                                       |

#### 8.4.3 Outcome of AEs

All subjects who have reportable AEs, whether considered associated with the use of the clinical trial medication or not, must be monitored to determine the **outcome**. The clinical course of the AE will be followed up until resolution or normalization of changed laboratory parameters or until it has changed to a stable condition. This also holds for ongoing AEs/SAEs of withdrawn subjects.

The **outcome** of an AE at the time of the last observation will be classified as:

|                                     |                                                                                                                                                                                          |
|-------------------------------------|------------------------------------------------------------------------------------------------------------------------------------------------------------------------------------------|
| Recovered / resolved:               | All signs and symptoms of an AE disappeared without any sequelae at the time of the last interrogation.                                                                                  |
| Recovering / resolving:             | The intensity of signs and symptoms has been diminishing and / or their clinical pattern has been changing up to the time of the last interrogation in a way typical for its resolution. |
| Not recovered / not resolved:       | Signs and symptoms of an AE are mostly unchanged or worsened at the time of the last interrogation.                                                                                      |
| Recovered / resolved with sequelae: | Actual signs and symptoms of an AE disappeared but there are sequelae related to the AE.                                                                                                 |
| Fatal:                              | Resulting in death. If there is more than one adverse event only the adverse event leading to death (related) will be characterized as 'fatal'.                                          |
| Unknown                             | The outcome is unknown or implausible and the information cannot be supplemented or verified.                                                                                            |

#### 8.4.4 Action taken with the IMP

The **action taken with the IMP** will be assigned to one of the following categories:

|                   |                                                                                      |
|-------------------|--------------------------------------------------------------------------------------|
| Dose not changed: | No change in the dose of the IMP.                                                    |
| Dose reduced:     | Reduction in the dose of the IMP.                                                    |
| Drug withdrawn:   | Discontinuation of the IMP.                                                          |
| Unknown:          | The information is unknown or implausible and it cannot be supplemented or verified. |
| Not applicable:   | The question is implausible (e.g. the subject is dead).                              |

|                                                                    |                                              |                                |
|--------------------------------------------------------------------|----------------------------------------------|--------------------------------|
| Clinical Trial Code: PROTECT
EU trial number: 2022-502332-39-00 | Trial Protocol
(Version 06; (01.10.2024)) | Page 87 of 110
CONFIDENTIAL |
|--------------------------------------------------------------------|----------------------------------------------|--------------------------------|

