| Febrile neutropenia                                                                                                                                                   | Interrupt study drug until resolution to $\leq$ grade 1 or screening level. If resolution occurs $\leq 7$ days, reintroduce study drug at the dose level prior to interruption. If                                                                                                                                                                                                                                    |

|                                                                    |                                              |                                |
|--------------------------------------------------------------------|----------------------------------------------|--------------------------------|
| Clinical Trial Code: PROTECT
EU trial number: 2022-502332-39-00 | Trial Protocol
(Version 06; (01.10.2024)) | Page 62 of 110
CONFIDENTIAL |
|--------------------------------------------------------------------|----------------------------------------------|--------------------------------|

|                                                                          |                                                                                               |
|--------------------------------------------------------------------------|-----------------------------------------------------------------------------------------------|
|                                                                          | resolution occurs > 7 days, or event reoccurs within 28 days, reduce subsequent doses to 50%. |
| Any hematologic toxicity requiring study drug interruption for > 28 days | Discontinue study drug                                                                        |

Re-initiation of treatment with the IMP will be done under close and appropriate clinical and/or laboratory monitoring if according to the investigator's medical judgment the concerned event is unlikely to be related to the IMP and if the selection criteria for the trial are still met. For all temporary treatment discontinuations, duration must be recorded by the investigator in the appropriate pages of the eCRF.

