### 7.1 Temporary Discontinuation from Treatment with the IMP

Temporary treatment (IMP) discontinuation at the discretion of the investigator is defined as one or more doses not administered to the subject.

Temporary treatment discontinuation may be considered by the investigator because of the following:

- Sirolimus may affect the response to vaccination. Sirolimus should be paused 2 weeks before until 2 weeks after receiving a live vaccine. The SmPC of Sirolimus recommends avoiding live vaccines during treatment with Sirolimus. Individual risks/ benefits should be discussed with infectious disease specialists.
- Surgical interventions: Treatment with sirolimus may affect wound healing. We recommend pausing treatment 14 days before until 14 days after elective surgical interventions. For non-elective interventions, therapy should also be paused until 14 days after the procedure.
- For a single grade 3 adverse event or for less serious adverse events, e.g. uncomplicated (viral) infections, sirolimus can be temporarily discontinued at the discretion of the investigator (for details see chapter 5.5.3)
- Grade 4 adverse event (for details see chapter 5.5.3)

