## 8.6 Period of Observation and Documentation

### 8.6.1 Adverse Events (AEs)

**AEs** will be ascertained by the investigators using non-leading questions, noted as spontaneously reported by the caregiver(s) of the subjects to the medical staff at any time during the trial or observed at any of the clinical trial visit.

The observational period begins with the signature of the informed consent form (ICF) and ends with the end of trial visit (V13). Same applies for SAEs/AESIs. AEs will be interrogated for at each contact between the responsible investigator and the caregiver(s) of the clinical trial subject. Thereafter, the investigator does not need to actively monitor subjects for adverse events. However, if the investigator becomes aware of a serious adverse event with a suspected causal relationship to the IMP (SAR) that occurred after the end of the observational period he or she shall report the SAE without undue delay to the Sponsor, as long as the clinical trial is still ongoing. This kind of SARs is also to be documented in the eCRF.

AEs will be documented in the subject file and in the eCRF. AEs will be reported with patient number, start and end date, description, grading, seriousness, relationship, action taken and outcome. These are the parameters that can be found on the standard AE-eCRF page. If applicable, all medical diagnoses or symptoms occurring prior to the beginning of the period of observation and documentation will be recorded in the eCRF as medical history.

The following general rules apply to the documentation of the AEs and SAEs: The start date of a SAE must not be earlier than that of the corresponding AE. The end date of a SAE is typically the same as that of the AE. The end date of the SAE must not be later than the end date of the corresponding AE. AEs and SAEs that are ongoing at the time of death are considered not resolved or resolving.

All SAEs/AESIs and their relevance for the benefit-risk assessment of the clinical trial will be evaluated continuously during the clinical trial and for the final report. All SAEs/AESIs will be documented in the eCRF and in the 'SAE/AESI Report Form' (see section 8.7.1).

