## 9.5 Secondary Analyses

### 9.5.1 Main Trial Analyses

**All secondary parameters** will be analyzed for the FAS.

BSID-III cognitive scale at the age of 1 year will be analysed similar to the primary endpoint. In addition, the BSID-III cognitive scale and important subscales will be analysed descriptively by group and time point using standard descriptive measures for continuous variables. The VABS total scales, important VABS subscales, ADOS total scales, and important ADOS subscales will be analysed descriptively by group and time point using standard descriptive measures for continuous variables, as well. In addition, for cognitive impairment and autism spectrum disorders at 1 and 2 years of age, 95% CIs will be calculated by treatment group in addition to the relative frequencies using the method of Wilson. The M-CHAT-R/F and TAND will be analysed descriptively by group and time point using absolute and relative frequencies.

The MRI characteristics (as defined in Section 6.8) will be analysed by group and time point, i.e. randomization (last image before randomization) and at 2 years of age  $\pm$  6 months.

Seizure characteristics, EEG characteristics, abdominal sonography characteristics, ECG and echocardiography characteristics (as defined in Section 6.8) will be analysed by treatment group and time point (if applicable).

All **safety parameters** will be analyzed for the SAF. Only treatment emergent-event adverse events will be analysed. Frequencies (number of adverse events & number and percentage of patients with at least one adverse event) will be tabulated according to system organ class and preferred term. One table each will be created showing: all adverse events, all serious adverse events, all adverse events of special interest, all non-serious adverse events, all adverse events leading to death, all adverse events related to the treatment (treated group only), all adverse events by severity. In addition, adverse events and special situations will be analysed by categories defined in the eCRF (number of events & number and percentage of patients with at least one event).

For laboratory values and vital signs, the analyses will be conducted by visit and shift tables comparing all values by visit to the relevant baseline value will be displayed additionally.

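### The action-taken list in 8.4.4 has no code for temporary interruption, so an adverse event that pauses sirolimus and resumes at the same dose cannot be coded correctly

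*Protocol*

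**What the plan says.** Section 8.4.4 gives a closed list: the action taken "will be assigned to one of the following categories". *Dose not changed* is defined as "No change in the dose of the IMP", *dose reduced* as "Reduction in the dose of the IMP" and *drug withdrawn* as "Discontinuation of the IMP". *Unknown* is for missing or implausible information, and *not applicable* for cases where the question makes no sense, such as after death.

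Other sections treat a pause as an action in its own right. Section 7.1 defines it: "Temporary treatment (IMP) discontinuation at the discretion of the investigator is defined as one or more doses not administered to the subject". Section 7.2 defines permanent discontinuation separately. Table 6 in section 5.5.3 sets out when the drug is interrupted, reduced or stopped for toxicity, and the text after it adds: "For all temporary treatment discontinuations, duration must be recorded by the investigator in the appropriate pages of the eCRF".

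The action taken is a field of the adverse event record. Section 8.6.1 states: "AEs will be reported with patient number, start and end date, description, grading, seriousness, relationship, action taken and outcome". Section 9.5.1 then says that "adverse events and special situations will be analysed by categories defined in the eCRF".

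**The concern.** The code list does not match the actions that the protocol itself prescribes. For an event that pauses sirolimus and restarts it at the same dose, a site can defend *dose not changed*, because the dose before and after is equal. It can also defend *drug withdrawn*, because section 7.1 uses the word discontinuation for a pause. Neither describes what happened, and nothing in the protocol settles the choice across the 17 to 20 sites.

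Adverse events are a listed secondary endpoint, and Rapamune has no approval for this age group and indication (section 5.2.1). Whether toxicity led to a pause or to a permanent stop is a natural tolerability question here. A summary built on this field could not answer it. This is a rule for data capture, so an analysis plan written later cannot restore a category that sites were never offered.

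**Working it through.** No power or sample-size figure is involved, and the plan states no figure to reproduce. The check is a row count of Table 6 set against the codes in 8.4.4.

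**Step 1: classify the rows of Table 6.** The febrile neutropenia row runs over a page break and counts once.

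| First response in Table 6 | Rows | Which |
|---|---|---|
| Interrupt or hold; same-dose restart possible | 6 | pneumonitis grade 2; mucositis grade 2 and 3; AST/ALT grade 3; thrombocytopenia grade 3; neutropenia or anaemia grade 3; febrile neutropenia |
| Interrupt or hold; no same-dose restart | 5 | pneumonitis grade 3; AST/ALT grade 4; any other grade 4; thrombocytopenia grade 4; neutropenia or anaemia grade 4 |
| Discontinue at once | 5 | pneumonitis grade 4; recurrent grade 4 after reduction; clinical liver failure; non-haematologic interruption over 28 days; haematologic interruption over 28 days |
| Maintain or no action | 3 | AST/ALT grade 1 or 2; thrombocytopenia grade 2; neutropenia or anaemia grade 2 |

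Total: 6 + 5 + 5 + 3 = 19. Interrupt or hold: 6 + 5 = 11, and 11/19 = 58%. Interruption is the most frequent response in the table.

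**Step 2: match each course of events to a code.**

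- *Pause, then the same dose* (possible in 6 rows). *Dose not changed* hides the missed doses. *Dose reduced* is false. *Drug withdrawn* is wrong if it means a permanent stop. *Unknown* and *not applicable* do not apply, because the action is known. No code fits.
- *Pause, then 50%* (the 5 rows above, and the 6 same-dose rows when resolution is slow or the event recurs). *Dose reduced* is right for the end result. Only one code may be chosen, so the pause is not visible in this field.
- *Pause, then discontinuation* (pneumonitis grade 3 and AST/ALT grade 4 when resolution is slow). *Drug withdrawn* fits.

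**Step 3: compare the wording.** Section 7.1 speaks of temporary discontinuation and 7.2 of permanent discontinuation. Section 8.4.4 says discontinuation without either qualifier, so its text does not tell a reader which is meant.

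**Step 4: see what other records supply.**

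- The introduction to section 7 requires the date and one primary reason for a withdrawal in the eCRF.
- Section 6.8 (Therapy) requires the current dose and all adjustments at each visit.
- Section 5.5.3 requires the duration of every temporary discontinuation.

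None of these provisions asks for a link from a pause to an adverse event, and the field list in 8.6.1 contains none. Pauses for live vaccines and for surgery (5.5.3 and 7.1) are temporary discontinuations too, so the duration records mix causes.

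**The case against.** The strongest reply is that the gap is narrow and the information largely exists elsewhere. Much of this stands, and it rules out four stronger readings.

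- **A reader might infer that every event that interrupts sirolimus must be coded as *dose not changed* or *drug withdrawn*.** That is not so. When dosing resumes at 50%, *dose reduced* is available and correct for the outcome. Only same-dose restarts are left without a fitting code.
- **A reader might infer that the trial's count of permanent discontinuations would be wrong.** The documents do not support this. Permanent stops are recorded separately with date and primary reason, so they can be counted without the adverse event code. Only a table built on that code alone would be exposed.
- **A reader might infer that the planned safety tables or the DSMB review are compromised.** Section 9.5.1 names seven tables: all events, serious, special interest, non-serious, leading to death, related, and by severity. None is by action taken. The link is the general sentence on eCRF categories. Section 12.5.1 gives the DSMB the task of assessing safety but does not say that it uses this field.
- **A reader might take Table 2 as the frequency of the problem.** Under 24 months it shows neutropenia in 3/14 (21%) to 5/12 (42%) and anaemia in 8/14 (57%) to 11/12 (92%) of those tested. These are all grades, whereas Table 6 takes no action at grade 2 and interrupts for cytopenias from grade 3. Section 1.3.7 reports no grade 3 or 4 events in one cohort of 17, grade 3 events in 7 of 45 infants (7/45 = 16%) in another, and mostly grade 1 and 2 events in the cohort behind Table 2. None of these gives an interruption rate.

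It is also fair that inconsistent coding between sites is a possibility, not an observation, and that the eCRF and its completion instructions are not at hand. If the eCRF already offers an interruption code, only the protocol needs aligning.

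The reply does not remove the core point. The list is closed, it omits the protocol's most frequent response to toxicity, and a recorded duration without a cause does not show which event led to the pause. Matching on time could recover some cases, but not reliably where events overlap or where the pause was for a vaccine or surgery.

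**Conclusion.** The point holds in a limited form. Section 8.4.4 has no code for temporary interruption, although 11 of 19 Table 6 rows and section 7.1 provide for it. An event followed by a same-dose restart, a path in 6 rows, has no fitting code. An event followed by a 50% reduction loses its interruption in this field. *Drug withdrawn* does not separate temporary from permanent discontinuation.

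The effect is confined to the action-taken field and any tabulation of it under 9.5.1. The primary endpoint, the seven named safety tables and the dosing record are unaffected. The number of events affected cannot be derived from the documents, because they give no rate of interruption.

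This rests on two assumptions: that the eCRF page follows the list in 8.4.4, and that one code is entered per event, as its wording indicates. The change should be made, because following the rule as written produces a wrong safety code and the correction is cheap.

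**What to change.** 1. Add *drug interrupted* (temporarily stopped) to 8.4.4 and to the adverse event page of the eCRF.
2. Define *drug withdrawn* as permanent discontinuation under section 7.2.
3. State how to code an event with both a pause and a later reduction: either allow two actions, or name the code to use and let the pause record carry the interruption.
4. Record the reason for each pause (adverse event, vaccine, surgery, other) and, where it is an adverse event, which one.
5. Query events already entered for participants with a recorded pause. Section 5.5.3 requires durations, not dates, so sites may have to confirm the match.

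The cost is one eCRF code, a reason field for pauses, a short wording change and limited recoding, which grows with each event entered. The change reconciles 8.4.4 with Table 6, 7.1 and 7.2 and alters no dose or clinical rule.

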#### 8.4.5 Countermeasures

The term “**countermeasures**” refers to the specific actions taken to treat or alleviate adverse events or to avoid their sequelae. The following categories will be used to classify the countermeasures taken for adverse events:

|                 |                                                                |
|-----------------|----------------------------------------------------------------|
| None:           | No action taken.                                               |
| Drug treatment: | Newly-prescribed medication or change in dose of a medication. |
| Others:         | Other countermeasures, e.g. an operative procedure.            |

#### 8.5 Special Situations Reporting

The following events are also to be immediately reported to the sponsor even if they do not result in an adverse event (for reporting obligations see section 8.7.1):

**Medication error:** This is an unintended failure in the IMP treatment process that leads to, or has the potential to lead to harm to the subject. This includes mistakes in the prescribing, dispensing, storing, preparation and administration of the IMP. The following deviations from the treatment are not regarded as medication errors:

- The medication was refused, spat out, or swallowed incompletely by the study participant.

**Misuse:** This refers to situations where the investigational medicinal product is intentionally and inappropriately used not in accordance with the terms of the trial protocol.

**Overdose:** This refers to the administration of a quantity of the investigational medicinal product given as repeated overdosing more than the double of intended dosage per administration. The following deviations are not regarded as overdose:

- Single overdosing up to double of intended dosage

**Use outside of what is foreseen in the protocol:** This relates to situations where the investigational medicinal product is used for a purpose being not in accordance with the indication defined in the trial protocol.

**Abuse:** This corresponds to the persistent or sporadic, intentional excessive use of the investigational medicinal product, which is accompanied by harmful physical or psychological effects.

